### Baseline assessments

3.11

Sociodemographic data are planned to be collected from the included patients, and also the data on duration of disease and previous herbal medicine treatments.

### Statistical analysis

3.12

The analysis will follow the principle of intention to treat (ITT). All statistical tests were conducted by two-sided tests and P values less than 0.05 were considered statistically significant. The description of quantitative indicators will calculate the number of cases, mean, standard deviation, median, minimum and maximum. Classification indicators are described by the number of cases and percentages of each category. For quantitative data, a mixed effect model was used to compare the change values of the two groups before and after treatment. The baseline score was taken as a covariable, and the grouping and central effect were considered in this analysis model. The dependent variable is the base change value of comparison point at each time point after treatment. Based on this model, the least square mean (LSMEAN) and the 95% confidence interval of the two groups will be calculated respectively. Kaplan–Meier method will be used to draw OS and PFS survival curves, and log-rank will be used to test the differences between the two groups. The differences of OS and PFS will be discussed in subgroup analysis according to age, sex, left and right colon, gene status, and microsatellite status.

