**Methods::**

Multicenter RCT with two parallel groups in three hospitals planning to recruit 120 CRC patients with the type of damp-heat will be conducted. The control group will be treated by basic antitumor therapy and the treatment group will use modified GGQL formula plus basic antitumor therapy. The primary outcomes will be quality of life, TCM symptom score, PFS and OS, and the secondary outcomes will be performance status, size of tumor, tumor marker in the serum, tumor microenvironment and immune status. All analyses will be based on an intention-to-treat principle. This study was approved by the Human Research Ethics Committee of Shanxi Province Hospital of Traditional Chinese medicine (2021Y-06017). The results will be published in relevant journal.

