### Primary outcome measures

3.7

1.Quality of life: measured by SF-36 at the baseline, week 6 of treatment, and week 12 of treatment;2.TCM symptom score: measured by the form of TCM symptom at the baseline, week 6 of treatment, and week 12 of treatment;3.Progression-free survival (PFS): measured by follow-ups;4.Overall survival (OS): measured by follow-ups.

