### Sample size calculation

3.10

The number of participants is capable to detecting according to the results of the previous study (1-year survival rate was 80% and the median overall survival was 25 months in the treatment group; 75% and 22 months respectively in the control group) with an alpha error of 0.05 and beta error of 0.2. Considering the 20% drop-out rates, the sample will be composed of 120 participants randomized into two groups.

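### Four unranked primary outcomes are each judged at an undivided two-sided 0.05, so if any one may count as success the false-positive risk is about 14.5–18.5%, not 5%

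*Protocol article*

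**What the plan says.** The Abstract (Methods) states: "The primary outcomes will be quality of life, TCM symptom score, PFS and OS". Section 3.7 (Primary outcome measures) lists the same four with none marked as leading. Two of them are measured repeatedly: "Quality of life: measured by SF-36 at the baseline, week 6 of treatment, and week 12 of treatment" and "TCM symptom score: measured by the form of TCM symptom at the baseline, week 6 of treatment, and week 12 of treatment".

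Section 3.12 (Statistical analysis) sets the significance rule: "All statistical tests were conducted by two-sided tests and P values less than 0.05 were considered statistically significant". The quantitative outcomes go into a mixed effect model, of which it says: "The dependent variable is the base change value of comparison point at each time point after treatment". For OS and PFS, "log-rank will be used to test the differences between the two groups".

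Section 3.10 (Sample size calculation) works "with an alpha error of 0.05 and beta error of 0.2". It uses survival figures only and does not divide alpha among the four outcomes.

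The article does not say which primary outcome leads, in what order they are tested, how alpha is shared, or whether one, some or all of the four must succeed.

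**The concern.** A primary outcome decides whether the treatment is called effective. With four of them, each significant in its own right at 0.05, a trial of an ineffective formula has four chances of a positive primary result. The 5% in Sections 3.10 and 3.12 then applies to each test separately and not to the primary conclusion.

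Because no success rule is written down, the choice of which outcome carries the conclusion stays open until the data have been seen. A nominally significant TCM symptom score could be reported as primary success while PFS and OS show nothing, and nothing in the text would rule that out.

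**Working it through.** **The plan's own figure.** The article gives no family-wise error rate. Its only error figure is 0.05, used undivided in Sections 3.10 and 3.12, so there is no family-wise figure to reproduce.

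**Inputs from the article.** Four primary outcomes (Abstract; Section 3.7). Two post-baseline visits, weeks 6 and 12, for SF-36 and TCM score (Section 3.7). Two-sided 0.05 for all tests, with log-rank for both PFS and OS (Section 3.12). 120 patients, 20% drop-out and power 1 − 0.2 = 0.80 (Section 3.10). Allocation 1:1 (Section 3.5).

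**Assumptions, not in the article.** No outcome is truly affected. Success on any one primary counts. Correlations between the test statistics are not given, so they are varied from 0 to 0.7.

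**One test per outcome (4 tests).** If independent:

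1 − 0.95^4 = 1 − 0.8145 = 0.185, or 18.5%.

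The upper bound under any dependence is 4 × 0.05 = 20%. With correlated tests (multivariate normal simulation, 1,000,000 draws, critical value 1.96):

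| SF-36 with TCM | PFS with OS | Scores with survival | At least one false positive |
|---|---|---|---|
| 0.2 | 0.2 | 0.1 | 18.2% |
| 0.3 | 0.3 | 0.3 | 17.3% |
| 0.5 | 0.5 | 0.3 | 16.7% |
| 0.5 | 0.5 | 0.5 | 15.6% |
| 0.7 | 0.7 | 0.5 | 14.5% |

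**Both visits tested for the two scores (2 × 2 + PFS + OS = 6 tests).** If independent:

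1 − 0.95^6 = 1 − 0.7351 = 0.265, or 26.5%.

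The upper bound is 6 × 0.05 = 30%. In the same kind of simulation:

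| Between visits | SF-36 with TCM, same visit | PFS with OS | Scores with survival | At least one false positive |
|---|---|---|---|---|
| 0.5 | 0.3 | 0.3 | 0.1 | 24.7% |
| 0.6 | 0.5 | 0.5 | 0.2 | 22.9% |
| 0.7 | 0.5 | 0.5 | 0.3 | 21.8% |
| 0.7 | 0.7 | 0.7 | 0.5 | 18.9% |

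**After correction.** At 0.05/4 = 0.0125 each, which is also Holm's first step, 1 − (1 − 0.0125)^4 = 0.049 if independent, and 4.0–4.9% over the correlations tried. A fixed testing order holds 5% with 0.05 at each step.

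**Price of Holm's first step, for a score outcome.** Detectable standardised difference = (z for alpha + z for power) × √(2/n per arm). With 20% drop-out, n = 120 × 0.8 / 2 = 48; with everyone analysed, n = 60.

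- n = 48, alpha 0.05: (1.960 + 0.842) × √(2/48) = 0.57
- n = 48, alpha 0.0125: (2.498 + 0.842) × √(2/48) = 0.68
- n = 60, alpha 0.05: (1.960 + 0.842) × √(2/60) = 0.51
- n = 60, alpha 0.0125: (2.498 + 0.842) × √(2/60) = 0.61

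**The case against.** The strongest reply is that this is a condensed article and that a full protocol or analysis plan may contain a multiplicity rule. The P < 0.05 sentence is, on this view, an ordinary convention and not a definition of trial success. If all four outcomes had to succeed, the error rate would not be inflated at all.

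Part of this stands. The article does not say that one significant primary is enough, so every figure above is conditional on that reading. The objection does not remove the point, because the article is not merely silent: it fixes four equal primaries and one threshold for all tests. A separate plan that added an order or an adjustment would have to override that threshold.

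A reader might also infer more than the text supports:

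- **That weeks 6 and 12 are certainly tested separately.** Section 3.12 models change at each visit, but does not say whether the groups are compared by one overall effect or visit by visit. The six-test range is a plausible reading only.
- **That 17% is a floor.** With one test per outcome, that needs low to moderate correlation. PFS and OS may well be strongly related, as may the two scores, and 14.5% is then reachable.
- **That the several SF-36 scores multiply the count further.** The article does not say how SF-36 is scored, so no larger count can be derived from it. Leaving the scoring to a fuller document is not itself an error.
- **That the lack of blinding (Section 3.5) strengthens this point.** Expectation effects on subjective scores are a separate source of bias, which no multiplicity adjustment removes.

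**Conclusion.** The point holds in a conditional form. Followed as written, the plan lets any of four unranked primaries be called significant at 0.05 and does not hold 5% for the primary conclusion. If one success suffices, the false-positive risk is 18.5% under independence and about 14.5–18% over the assumed correlations, roughly three to four times the stated level. If the two scores are also tested at both visits, it is about 19–26.5%. The number of outcomes and the threshold come from the article; the correlations and the any-one-counts rule are assumptions. The rule should be settled before outcome data are compared between arms, since a choice made afterwards would not be credible.

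**What to change.** Name one SF-36 score and one time point, for example week 12, for both SF-36 and TCM score, and make week 6 secondary. Then write one of two rules into Section 3.12:

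1. Keep one outcome primary and test the others in a fixed prespecified order, each at two-sided 0.05, stopping formal claims at the first non-significant result.
2. Keep all four primary and apply Holm at an overall two-sided 0.05, with success defined as at least one Holm-adjusted rejection.

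The significance sentence in Section 3.12 should refer to the chosen rule, and the Abstract and Section 3.7 should match it.

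This takes a few sentences and no new data. The fixed order needs no stricter threshold, but an early failure blocks later claims. Holm's first-step threshold of 0.0125 raises the detectable standardised difference from about 0.57 to 0.68 with 48 per arm, or from about 0.51 to 0.61 with 60 per arm.

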### Randomization and blinding

3.5

The process of randomization will be carried out by stratified block randomization method with the block size setting as four and six, and the center was taken as the stratified factor. The participants will be divided into the treatment group and the control group randomly with a ratio of 1:1. We will use the ‘Proc plan’ of SAS9.3 statistical analysis software for generating the random scheme. The central randomization system for clinical research (provided by the Oncology Department of Shanxi Hospital of Traditional Chinese Medicine) will be used for randomization. When qualified patients are enrolled, the randomization personnel or clinical investigators in each center will log into the central randomization system through telephone or Internet to apply for the randomization number.

Because of no herbal medicine used in the control group, it will hardly to blind the doctors and patients involved in this RCT.

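### OS and PFS are to be compared by a log-rank test with no centre strata and no named effect measure, although randomisation is stratified by centre

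*Protocol article*

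**What the plan says.** Section 3.5 (Randomization and blinding) describes a "stratified block randomization method with the block size setting as four and six", and adds that "the center was taken as the stratified factor". The abstract gives three hospitals. OS and PFS are two of the four primary outcomes (section 3.7).

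Section 3.12 (Statistical analysis) handles the two kinds of primary outcome differently:

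- **Scores (quantitative data).** A mixed model is used, with baseline as covariate, and "the grouping and central effect were considered in this analysis model", which I read as treatment group and centre. From it, "the least square mean (LSMEAN) and the 95% confidence interval of the two groups will be calculated respectively".
- **OS and PFS.** The Kaplan-Meier "method will be used to draw OS and PFS survival curves", and "log-rank will be used to test the differences between the two groups". Subgroup analyses follow. No strata, centre term, regression model, hazard ratio or confidence interval is mentioned.

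**The concern.** An analysis should normally reflect the factors used to stratify randomisation. Blocking within centre balances the arms within each hospital. If hospitals differ in prognosis, that balance makes the log-rank statistic vary less than its unstratified variance formula assumes. The plain test then rejects too seldom and gives away power. The same section takes centre into account for the scores, so the survival primaries are handled less carefully than the questionnaire outcomes in the same trial.

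The second part is the effect measure. A log-rank P value does not say how large the effect is or how precisely it is known. With few deaths, a non-significant P is compatible with both a large benefit and a large harm, and only an interval shows that.

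**Working it through.** The plan gives no figure for this point, so there is none to reproduce. Stratifying the test does not change N = 120. Whether 120 follows from the inputs in section 3.10 is a separate matter, which this change does not mend.

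**1. What the unstratified test costs**

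Inputs from the article: 120 patients, three centres, 1:1 allocation, blocks of four and six within centre, two-sided 5% level, control median OS 22 months.

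Assumptions, none of them in the article: 40 patients per centre, exponential survival, uniform accrual over 24 months plus 12 months of further follow-up, no drop-out, and the control medians by centre shown below. The hazard ratio of 0.88 is the ratio of the planning medians, 22/25. The value 0.6 is an assumed larger effect.

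Both tests use Z = ΣU / √ΣV, where U sums observed minus expected deaths in the treated arm and V sums p(1 − p), with p the treated share of those at risk at each death. The plain test pools all centres. The stratified test computes U and V within each centre and then adds them. There were 8,000 runs per row.

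| Control medians by centre (months) | Hazard ratio | Plain test rejects | Stratified test rejects |
|---|---|---|---|
| 22 / 22 / 22 | 1 | 5.0% | 5.3% |
| 22 / 22 / 22 | 0.88 | 8.5% | 8.4% |
| 22 / 22 / 22 | 0.6 | 45.3% | 44.5% |
| 16 / 22 / 30 | 1 | 4.9% | 5.2% |
| 16 / 22 / 30 | 0.88 | 8.3% | 8.5% |
| 16 / 22 / 30 | 0.6 | 44.7% | 45.5% |
| 11 / 22 / 44 | 1 | 3.5% | 5.0% |
| 11 / 22 / 44 | 0.88 | 5.3% | 8.0% |
| 11 / 22 / 44 | 0.6 | 39.8% | 45.9% |

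The simulation standard error of a single rate is √(0.05 × 0.95 / 8000) ≈ 0.24 points near 5% and √(0.45 × 0.55 / 8000) ≈ 0.56 points near 45%. The first six rows therefore show no difference of practical weight. The last three do: 5.0 − 3.5 = 1.5 points of unused type I error, and 45.9 − 39.8 = 6.1 points of power at a hazard ratio of 0.6. With no centre effect, stratifying costs at most 45.3 − 44.5 = 0.8 points.

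**2. What a P value alone leaves out**

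The article gives no event count and no end of survival follow-up, so the number of deaths can only be assumed. Take 60 per arm, exponential survival with medians 22 and 25 months, uniform accrual over 24 months and no drop-out, with λ = ln 2 / median.

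- Cut-off at month 24: P(death) = 1 − (1 − e^(−24λ)) / (24λ), which is 0.298 (control) and 0.270 (treatment). Deaths: 60 × (0.298 + 0.270) ≈ 34.
- Cut-off 12 months later: P(death) = 1 − (e^(−12λ) − e^(−36λ)) / (24λ), which is 0.519 and 0.476. Deaths: 60 × (0.519 + 0.476) ≈ 60.

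With SE(log HR) ≈ 2/√deaths, an observed hazard ratio of 0.88 would have these 95% intervals:

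- 34 deaths: SE = 0.343; exp(ln 0.88 ± 1.96 × 0.343) = 0.45 to 1.72.
- 60 deaths: SE = 0.258; exp(ln 0.88 ± 1.96 × 0.258) = 0.53 to 1.46.

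The exponential form is itself a simplification: a 22-month median implies 0.5^(12/22) = 68.5% one-year survival, against the 75% in section 3.10. The count for the early cut-off may therefore be somewhat too high.

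**The case against.** The strongest reply is that this is a condensed article and the statistical analysis plan is not shown. The strata of a log-rank test, a hazard ratio and its interval are details often left to that plan. The article never calls the test unstratified, and Kaplan-Meier curves can supply medians and one-year survival, the measures used in section 3.10. Most of this stands. It is why the point is that no effect measure is *named*, not that none will be given. What remains is that section 3.12 goes into enough detail to name centre and confidence intervals for the scores and then gives neither for the survival primaries.

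It is also fair to say that a large loss needs a four-fold spread in centre medians. Nothing in the article suggests one: all three sites are oncology departments in Taiyuan. That stands too, and it limits the weight of the point.

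The wide intervals reflect the small number of deaths. A Cox model displays that imprecision but does not cure it.

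A reader might go further on subgroups and infer, from the statement that "The differences of OS and PFS will be discussed in subgroup analysis according to age, sex, left and right colon, gene status, and microsatellite status", that every level of five factors will be tested separately at 5%. The article does not say so. It gives no age cut-point, does not define gene status, and neither describes separate tests nor excludes interaction tests. No false-positive rate can be computed from it, and I make no claim there.

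**Conclusion.** The point holds as a minor one. As written, the comparison of OS and PFS does not carry the stratification factor of the randomisation, although the model for the scores does, and no effect measure is named for either endpoint.

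A reader might infer that the log-rank result would be invalid. It would not: in none of the simulated settings did the plain test inflate type I error. The loss is about 6 points of power at a hazard ratio of 0.6 if centre medians are as far apart as 11, 22 and 44 months, and under 1 point with no or moderate centre differences. These sizes rest on assumed centre medians, equal centre sizes, exponential survival and 12 months of follow-up after accrual. They were worked out for OS-like medians; the article gives no PFS rates, so PFS was not simulated. The range of 34 to 60 deaths is likewise an assumption about when follow-up ends.

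**What to change.** In section 3.12, replace the sentence on the survival comparison with text to this effect: *OS and PFS will each be compared between groups by a two-sided log-rank test stratified by centre. The treatment effect will be reported as a hazard ratio with 95% confidence interval from a Cox model with treatment group as covariate, stratified by centre. Kaplan-Meier curves will be shown by group.* If the statistical analysis plan already says this, bring the protocol text into line with it. Because treatment is open-label, settle the wording before any outcome is compared by group.

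The cost is a change of wording. Centre is already recorded for randomisation, no new data or patients are needed, and three strata cost almost no power even if the centres turn out alike.

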### Secondary outcome measures

3.8

1.Performance status: measured by Karnofsky score at the baseline, week 6 of treatment, and week 12 of treatment;2.Size of tumor: measured at the baseline, week 6 of treatment, and week 12 of treatment;3.Tumor marker in the serum: measured at the baseline, week 6 of treatment, and week 12 of treatment;4.Tumor microenvironment: measured by vascular endothelial growth factor receptor (VEGFR) and Th1/Th2 in the serum at the baseline, week 6 of treatment, and week 12 of treatment;5.Immune status: measured by subset of the class of T-cells in the serum at the baseline, week 6 of treatment, and week 12 of treatment.

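### OS and PFS are compared by a log-rank test that uses neither centre nor any baseline prognostic factor: valid, but less precise than a short prespecified Cox model

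*Protocol article*

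**What the plan says.** Section 3.7 of the protocol article lists four primary outcomes, among them "Progression-free survival (PFS): measured by follow-ups" and "Overall survival (OS): measured by follow-ups". For these two, section 3.12 plans Kaplan-Meier curves and then says "log-rank will be used to test the differences between the two groups". It names no covariate, no stratification of the test and no effect measure such as a hazard ratio.

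The same section treats the quantitative outcomes differently: "The baseline score was taken as a covariable, and the grouping and central effect were considered in this analysis model". Patient factors enter the survival analysis in one place only: "The differences of OS and PFS will be discussed in subgroup analysis according to age, sex, left and right colon, gene status, and microsatellite status".

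On what is known before treatment, section 3.8 has "Performance status: measured by Karnofsky score at the baseline, week 6 of treatment, and week 12 of treatment", and section 3.11 says "Sociodemographic data are planned to be collected from the included patients". Age is not named in 3.11. It is implied by that sentence, by the age limit for eligibility and by the age subgroup. Section 3.5 stratifies the randomisation by centre and by no patient factor.

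**The concern.** The plan adjusts the score outcomes for baseline and centre, yet compares the two survival primaries without either kind of information. Subgroup analyses by age or tumour side do not help here, because they split the trial and neither sharpen the overall comparison nor correct it for imbalance. With 60 patients per arm and no patient factor balanced by design, the arms may differ by chance in prognosis, and the unadjusted hazard ratio carries that difference. Leaving out a truly prognostic factor also pulls the hazard ratio towards 1 and costs power. Karnofsky score, and by implication age, will be in the database anyway, so the loss is avoidable.

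**Working it through.** **Inputs from the protocol article.** 120 patients, 1:1, so 60 per arm; two-sided alpha 0.05; power 80%; median OS 25 against 22 months (3.10); recruitment over 24 months (4.1). The article gives neither the length of survival follow-up nor the prognostic strength of any factor. Both are assumed below.

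**The plan's own figure.** Under proportional hazards with exponential survival, the planned hazard ratio is 22/25 = 0.88 and ln 0.88 = -0.128. The events needed are 4 × (1.960 + 0.842)² / 0.1278² = 1,922. The stated 120 patients is not reproduced. Reading the 1-year rates as a hazard ratio, ln 0.80 / ln 0.75 = 0.776, still needs 487 events. Even 120 events would give 10.4% power at 0.88. This is a separate problem, but it decides how the results below should be read.

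**Chance imbalance.** Let σ be the SD of baseline prognosis on the log-hazard scale. The arm difference in prognosis has SD σ × √(2/60) = 0.183σ.

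- σ = 0.4: 0.073
- σ = 0.6: 0.110
- σ = 0.8: 0.146

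Against the planned effect of 0.128 this is 57% (0.073/0.128) to 114% (0.146/0.128).

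**Power.** Simulation with 8,000 trials per setting: 120 patients, exponential survival, control median 22 months, 24 months of accrual plus an assumed 12 months of follow-up, and one standard-normal covariate with the stated log hazard ratio per SD. The log-rank test is compared with a Cox model that includes the covariate. No centre effect and no drop-out were simulated, so the figures describe covariate adjustment only.

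| Hazard ratio | Prognostic strength | Log-rank | Adjusted Cox | Difference (points) |
|---|---|---|---|---|
| 0.88 | 0 | 8.1% | 8.0% | -0.1 |
| 0.88 | 0.4 | 7.6% | 7.9% | +0.3 |
| 0.88 | 0.7 | 7.2% | 7.9% | +0.7 |
| 0.88 | 1.0 | 6.6% | 7.8% | +1.2 |
| 0.45 | 0 | 78.0% | 77.0% | -1.0 |
| 0.45 | 0.4 | 76.1% | 78.5% | +2.4 |
| 0.45 | 0.7 | 69.6% | 78.6% | +9.0 |
| 0.45 | 1.0 | 62.2% | 80.6% | +18.4 |

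At a hazard ratio of 1, rejection was 4.7% to 5.1% across both tests. A smaller run (3,000 trials) at hazard ratio 0.5 gave gains of about 3, 9 and 19 points at strengths 0.4, 0.7 and 1.0.

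**Partial capture.** These gains assume that the model holds all of the prognostic information. In a PFS set-up (assumed control median 8 months, 6 to 24 months of follow-up, 20% drop-out, hazard ratio 0.5), full capture gave gains of about 5, 10 and 18 points at σ = 0.4, 0.6 and 0.8. With half the prognostic variance captured, the gains were about 2, 4 and 7 points.

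**The case against.** The log-rank test is a standard and valid choice, and baseline score is a natural covariate for a change score in a way that has no direct counterpart for survival. A condensed article may name its main test and leave an adjusted model to an analysis plan that is not shown. This is a fair reason to treat the point as an improvement and not as an error. It does not remove the point, because 3.12 does state the method for two primary outcomes and leaves out even the stratification factor.

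Three stronger readings are tempting, and the document supports none of them.

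- A reader might infer that the survival tests are unreliable or prone to false positives. Type I error is about 5% either way.
- A reader might infer that the missing adjustment is why the trial lacks power for survival. At the only effect the article plans, adjustment gains about 1 point or less. The shortfall comes from the sample size.
- A reader might take the 57% to 114% ratio to mean that imbalance can swamp any real effect. The ratio is large mainly because the planned effect is very small for 120 patients. Against a hazard ratio of 0.5 (log 0.693) the same imbalance is 11% to 21%. It is also below the ordinary standard error of the log hazard ratio, 2/√65 = 0.25 with about 65 PFS events under the assumed set-up.

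It is also tempting to put every subgroup factor into the model and to fault 3.11 for not listing them. Their collection is implied by the planned subgroups, and several such terms with levels for unknown status could overload a model with about 65 PFS events and fewer deaths.

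**Conclusion.** The point holds as a modest, low-cost improvement to a valid analysis. The stated comparison of OS and PFS ignores centre and the prognostic data already planned, and so gives up some precision and protection against chance imbalance (SD 0.07 to 0.15 on the log hazard ratio for an assumed σ of 0.4 to 0.8).

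The power at stake depends on assumed prognostic strength: about 1 point or less at the planned 0.88, and about 2 to 18 points at 0.45. The upper end needs a strength of 1.0 per SD; at 0.4 to 0.7 the gain is about 2 to 9 points. All of these shrink if Karnofsky score and age capture only part of prognosis, and a covariate with no prognostic value costs about 1 point at 0.45. Follow-up length and prognostic strength are assumptions throughout. Adjustment leaves the sample-size problem where it is.

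**What to change.** In 3.12, prespecify for OS and PFS a Cox model stratified by centre, with group, baseline Karnofsky score and age as covariates. Report the adjusted hazard ratio with its 95% CI, and keep the log-rank test and Kaplan-Meier curves as support. Keep tumour side, gene status and microsatellite status for the planned subgroups or a sensitivity analysis, outside the main model. Fix the covariates before outcome data are seen, since the trial is open-label and a later choice would carry little weight.

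The cost is a short addition to 3.12, and naming age in 3.11 would remove the need to infer it. The downside is that the hazard ratio becomes conditional on the covariates and depends on the model form, so it should stand next to the unadjusted result.
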